## Abstract

Our long-term goal is to foster genetically informed reproductive health knowledge and behaviors among young adults with sickle cell disease (SCD) or sickle cell trait (SCT) with a web-based, tailored, multimedia intervention called CHOICES. CHOICES is designed to help young adults with SCD or SCT preconception to gain knowledge of genetic inheritance, specify their reproductive health intentions (their parenting plan), and engage in reproductive health behaviors concordant with their parenting plan. In a previous study, we found high acceptability of both the e-Book (usual care control) and CHOICES interventions. We also found sustained (24 months), significant effects on knowledge but not on behavior, most likely because half of the recruited group was not *at risk* for their children inheriting SCD. Hence, we propose an adequately powered randomized controlled trial with the CHOICES intervention and an e-Book control to compare their effects on genetic inheritance knowledge and *at-risk* reproductive health behaviors (immediate posttest and at 6, 12, 18, and 24 months). We will conduct subgroup analyses to provide insight into the baseline knowledge and behavior as well as the intervention effects in different demographic or acceptability groups. Given the scalability and low cost of CHOICES, if proved to be effective, it can reach the affected population at low cost.

## Introduction

About 100,000 Americans have sickle cell disease (SCD) [1] and 3.5 million Americans have sickle cell trait (SCT) [2]. Annual U.S. healthcare costs for SCD are an estimated $2.4 billion [3], where each year 2,000 infants are born with SCD, [1] and over 60,000 infants are born with SCT [4]. Advances in newborn screening and treatments have reduced SCD morbidity and mortality [5], they, however, have not reduced uninformed inheritance of SCD, despite support in minority and healthcare communities for this goal [6]. Pregnancy outcomes are affected by insufficient or incorrect knowledge of one’s own or partner’s SCD/SCT status or SCD genetic inheritance [7–9]. Our long-term goal is to foster genetically-informed reproductive health knowledge and behaviors by young adults with SCD or SCT, which are single gene conditions that contribute to health disparities among minorities.

Responsive to RFA-HG-20-048, this study’s focus is to evaluate a scalable and low-cost process for follow-up care after communication of genetic results to individuals with SCD and SCT. In the U.S., the annual incidence of SCD nationally remains fairly constant [10], but worldwide SCD is projected to increase from 304,800 newborns born annually to 404,200 in 2050 [11]. SCD is the most common inherited lethal blood disorder, and is a costly, single-gene disease [12]. For the years 2000 through 2006, 15,277 American infants were diagnosed with SCD through newborn screening in 44 states. With current human diasporas and massive migration, genetic sickle cell pools from Africa, Middle East, Mediterranean, Central and South America, India, and a growing Hispanic population (1 per 1,000–1,400 births) contribute to the U.S. SCD population [12].

One of every 500 African Americans has SCD, and one of every 12 African Americans has SCT [1]. SCT is usually asymptomatic but, as an autosomal recessive condition, persons with SCT are at risk for having children with SCD if their reproductive partners have SCT or SCD. A rough estimation based on prevalence of SCT and SCD shows that if no action is taken, 0.94 in 500 births among African Americans will exhibit SCD, very close to the reported statistic of 1 in 500 births. Thus, these rates suggest that the *at-risk* population is not currently engaged in systematic efforts to reduce the risk of their children inheriting SCD, an important scientific premise for the proposed study. If both reproductive partners have SCD, for each pregnancy, there is 100% chance of the child having SCD. If one partner has SCD and one has SCT or another hemoglobinopathy, for each pregnancy, there is 50% chance of the child having SCD. If both partners have SCT, for each pregnancy, there is 25% chance of the child having SCD. If only one partner has SCD or SCT and the other partner has normal hemoglobin (Hb A), for each pregnancy, there is 0% chance the child will have SCD. Examples of two behaviors needed for a person with SCD or SCT to reduce the risk of having a child with SCD include [1] talking with one’s potential reproductive partner about sickle cell status and [2] seeking partners with Hb A. These behaviors, however, are not well-known or easy to accomplish for them or for any of the other 3 million Americans with one of the 10,000 other single-gene diseases (e.g., Huntington disease, Fragile X syndrome, cystic fibrosis, or muscular dystrophy) [13]. Study findings will provide evidence on how to mitigate uninformed inheritance of SCD worldwide and serve as an intervention model in follow-up to genetic counseling for other single-gene disorders.

In a series of four studies [14–17] we systematically established that the control and experimental interventions were relevant to the SCD community and that the participants were sufficiently engaged with the online computer delivery system. The CHOICES intervention significantly increased knowledge for young adults with SCD or SCT and this difference was sustained 24 months later. Intentions and behaviors were not significantly different between groups, most likely because half of the recruited group was not *at risk* for their children inheriting SCD. We concluded, therefore, that the proposed RCT should focus on individuals *at-risk* for having a child with SCD and whose parenting plan indicate that they want to avoid having a child with SCD and plan to have a child within the study period.

### Specific aims

Building on findings from the preliminary studies, we now propose a fully-powered RCT with refined methods and intervention enhanced with nudges and tailored boosters to compare effects of e-Book and CHOICES interventions on genetic inheritance knowledge (knowledge) and reproductive health behaviors (behaviors) (Fig 1). Using referrals from clinics, community-based organizations, transit advertising, and social media to recruit an adequately powered sample, we will use web-based data collection (SCKnowIQ—baseline, posttest, 6, 12, 18, 24 months) and intervention delivery (Fig 2). We will use multi-level regression analysis to examine the intervention effect on knowledge and behaviors (time *at-risk*). We will also explore predictors of outcomes. In a sample of 430 young adults (18–45 years of age, with SCD or SCT), specific aims are to:

#### Aim 1

Compare e-Book and CHOICES groups for effects on (a) knowledge (primary endpoint), and (b) *at-risk* behaviors (secondary endpoint) measured with the SCKnowIQ, over time (baseline, posttest, 6, 12, 18, 24 months). We hypothesize that (a) across all time points post baseline, there will be higher knowledge scores, and (b) lower percentage time with *at risk* behaviors (*at-risk* time) in the CHOICES than in the e-Book groups.

#### Aim 2

Explore the relationship between the demographic factors (e.g., gender, SC status), acceptability, and the Aim 1 endpoints (knowledge, behavior). We will conduct subgroup analyses to provide insight into the baseline knowledge and behavior as well as the intervention effects in different demographic and acceptability groups.

**Fig 1 pone.0294907.g001:**
[figure not shown]
Conceptual model and aims.

**Fig 2 pone.0294907.g002:**
[figure not shown]
Participant flow through the CHOICES sickle cell study.

As a genetic counseling follow-up model, CHOICES may translate into informed parental decisions and preparedness for the consequences of their preconception decisions and informed inheritance of SCD.

## Materials and methods

We are conducting a 2-year, randomized, longitudinal, repeated measures, controlled trial in 430 *at-risk* young adults with SCD (50%) or SCT (50%) to compare the effects of e-Book and CHOICES interventions on knowledge and behaviors across time (baseline, immediate posttest, 6, 12, 18, 24 months). We will provide boosters tailored to knowledge deficits at 6 and 12 months, but in the proposed RCT, we will also add monthly reinforcement nudges toward concordant behavior during the first 12 months. This clinical trial is registered at clinicaltrials.gov (NCT05292781), which exerted no control of this publication.

### Ethics statement

This study was approved by the Institutional Review Board (IRB) of the University of Florida to ensure ethical standards are upheld throughout the entire study.

### Setting and sample

The University of Florida (UF) will be the site for data collection, delivery of the intervention, and data analysis. Together, the UF Health Shands Hospital and UF Health Jacksonville Hospital serve approximately 933 patients with SCD. We will use Internet and remote technologies, which will allow participants to complete the study in their setting of choice (home, work, school, library, etc.) where Internet service is available. We will work with community based-organizations such as the Sickle Cell Disease Association of America (SCDAA) and its state-based chapters, the African American sororities and fraternities, and county extension agents to identify young adults with SCD or SCT not only from UF but also from Florida and other clinics and communities across the nation. Based on attrition in our prior community-based studies of adults with SCD or SCT, we will recruit 506 participants. With a projected 15% attrition rate, we expect 430 participants to complete the study.

### Eligibility criteria

Participants are eligible to participate in the CHOICES study if they meet the following eligibility criteria: Confirmed diagnosis of SCD, SCT, or another hemoglobinopathy, able and intends to conceive a child, wants to avoid the risk of having a child with SCD, are able to speak and read English, are at risk for having a child with SCD, and are between the ages of 18–45 years.

### Recruitment

We will use online recruitment processes including registration on Clinical Trials.gov and the SCDAA’s website. We will post recruitment information on Facebook, Instagram, TikTok, Twitter, Google+, other social media sites, and various Internet LISTSERVS to identify and recruit 506 young adults with SCD or SCT from across the U.S. (retaining 430). We used most of these processes and sites to recruit the Internet pilot study sample (*N* = 115 consented and *n* = 107 enrolled) that completed 24 months of follow-up at an 86% (*n* = 92) rate.

We will also distribute colorful posters and brochures in sickle cell clinics, at health fairs, university bulletin boards, churches, and other community-based sites. These posters differ from posters in our prior studies by intentionally utilizing language sensitive to individuals with SCD and SCT. These posters also utilize altruistic themes including descriptions on how their participation will make an impact. Additionally, our team members and Community Outreach Team will work directly with community-based organizations, healthcare networks, and churches to advertise the study within their networks, which are located throughout Florida and across the U.S. They and collaborators from clinics, SCD centers and organizations, and other community organizations (e.g., sororities, fraternities) will post recruitment flyers and encourage young adults to participate. These processes were effective in prior studies where we recruited 400+ participants mostly from IL but also from TX, NC, and CA. The participation of African American sororities and fraternities (collegiate and graduate chapters) is a new strategy for us and is likely to provide additional access to affected communities (college students, other young adults). African American sorority/fraternity members who are mothers and fathers of young adults will facilitate outreach to potential participants, especially those with SCT. These members live all over the U.S. and provide access not connected to healthcare settings. In our previous study, mothers who learned about the study were persistent in encouraging their young adult children to participate. Hence our ability to outreach to the sorority/fraternity members (who personally know their family members and friends affected by SCD or SCT) is likely to be successful.

We will also utilize transit interior bus advertisements in communities with large populations of individuals at risk for SCD or SCT. SCD advocates and influencers with substantial following on TikTok and Instagram will create videos to be released at different times promoting our study.

In summary, we will apply both previously tested and new strategies throughout the U.S., especially the Southern states that we intentionally did not sample in early studies so the powered efficacy study could access the states where nearly half of the individuals with SCD live [18]. Because Florida (FL) has a very large SCD population, we will leverage programs at the University of FL (UF) to identify and recruit participants with SCD or SCT. We will also leverage a nationwide resource (available in every state) for community outreach, the Agricultural Experiment Stations, whose mission is to educate their communities. The FL Institute of Food & Agricultural Sciences (IFAS) leads this work in FL and their Extension Agents and State Specialists will connect us to other stations and post flyers and inform their communities about the study.

Finally, we will expand outreach to the newborn screening programs, which are now available in all 50 states, to identify efficient processes for potential participants to obtain verification of their SCT status. These innovative outreach approaches to communities for the purpose of identifying individuals with SCT will strengthen the generalizability of study findings.

### Screening and consent

As an Internet-based study, all screening and consent processes are completed via the website to which the individual is directed to all the recruitment materials. The individual completes the screening questions, reads the online consent form, calls a number to discuss questions with a qualified staff member, and signs the consent by typing his/her name and clicking a statement of consent. Before the individual is randomized, however, we require the research specialist (RS) to speak to the consenting person via a phone call and upload of an official healthcare record documenting SCD or SCT status. The RS who will assist individuals in these screening and consent processes will be trained in Good Clinical Practices for research and IRB and HIPAA procedures. The training includes role-play and retraining if the staff makes mistakes in the process(es).

Safeguards for pregnant women who are not a targeted population (participants could be pregnant on enrollment or during the study), include a behavioral intervention with important information related to reproductive health decisions. Therefore, risks to pregnant women are minimal, and no greater than what they might face from daily life.

### Randomization

Randomization to e-Book and CHOICES groups will be stratified by SCD and SCT to assure that each group is balanced on this variable. Within each stratum, permuted block randomization with a block size of four will be performed to ensure group balance. The statistician will conduct the randomization and the programmer will implement it via computer code. All other team members will be blind to the group assignment with no access to the electronic group assignment table within the software application.

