### Procedures

The RS will develop Facebook pages for the study recruitment and retention processes. We will provide the potential participants with a link to the study website where they complete screening questions. RS receives confirmation of eligibility and sets up a time to discuss consent. Participants are sent a link to sign an online consent form, and have questions answered by the RS, who directs them to provide verification of SCD or SCT status. Once the RS receives the verification and approves the participants for participation, RS registers participants and participants are prompted to create a login and password on the CHOICES website. The software application randomizes the participants based on registration information after verified by the RS. The participants complete baseline measures and receive the CHOICES or e-Book based on group assignment. Table 1 lists a summary of the study data collection and intervention points, including boosters at 6 and 12 months and nudges monthly during the first 12 months of the study. For all intervention sessions, the experimental group reads or listens to the CHOICES intervention and the control group reads or listens to the usual care materials (e-Book) on the computer or mobile devices. At each follow-up visit, participants enter data with the SCKnowIQ data collection app (Table 1). Participants receive payments after each verified task via their selected method (mail, digital).

**Table 1 pone.0294907.t001:** CHOICES sickle cell study data collection and intervention summary.

Study Event	Time Points (mo)					
	Baseline	Posttest	6	12	18	24
**SCKnowIQ** Computerized Questionnaires—Sickle Cell:						
**Knowledge** Questionnaire	X	X	X	X	X	X
**Behavior** Tool	X	X	X	X	X	X
Demographic Questionnaire	X					
Intervention Acceptability		X				X
**CHOICES**—**Intervention** X initial; O nudges and booster tailored to most recent responses	X		O	O		
**e-Book**—**Intervention** X initial	X					
**Computer Acceptability Scale**		X				X

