The CHOICES program provides text, video clips, audio clips, graphics, cartoons, photos, and animations to help the participants overcome their knowledge gaps about SCD inheritance, available reproductive options, and state or role model the behavior steps to be taken to implement their parenting plans. There are extensive video clips of couples discussing their reproductive health choices to role model behaviors needed to implement their parenting plan, and how they feel about their choices and behaviors. For example, in one clip, a young couple breaks up after the young woman discloses that she has SCT and learns that her boyfriend also has SCT; she breaks up with him because she does not want any risk of having a baby with SCD and she would not consider other reproductive options, such as advanced reproductive technologies or pregnancy termination, particularly since she wants a large family. Another couple discusses being adoptive parents because they do not want to risk the woman’s health given that she has SCD. Video clips of these and other diverse scenarios bring reproductive health decisions to life serving to model the behaviors needed to implement the parenting plans and to supplement the text information. CHOICES includes skills training to promote mastery in performing the behavioral steps needed to implement the parenting plan, such as talking to one’s partner, getting tested for SCT, determining risk given a couple’s SCT or SCD status, selecting appropriate birth control methods, and adopting/fostering a child.

Therefore, the intervention is based on ELT to provide engaging and experience-based learning that also includes key elements important for concordant behavior. We will strengthen the behavioral component in the proposed study by adding reinforcement nudges and additional skills mastery components to the booster sessions. These additions will provide opportunities for skill development regarding concordant behavior that are needed to implement the parenting plan but were not performed in the previous 1–6 months. Boosters will also include positive reinforcement statements to recognize the participant’s concordant behavior successes and encouragement for success and importance for concordant behavior. Participants completed the intervention in 71.8 ± 28.7 minutes; each booster in 8 minutes, which will be longer with the refinements that we plan to add based on preliminary findings.

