The e-Book intervention contains information typically shared in clinical SCD care. It does not include other information related to the SCKnowIQ knowledge items or any of the behaviors needed to implement a parenting plan. The e-Book intervention will not include booster sessions, which differs from the preliminary study to minimize the repetition of genetic inheritance information, a key element of the CHOICES intervention. Although not as lengthy as CHOICES, the e-Book was completed at an average of 8.6 ± 2.8 minutes at baseline. It is sufficiently long, attractive, and engaging to retain participants randomized to the usual care control group; key factors for an adequate control condition. Interestingly, during the preliminary study and in interviews after the study, many e-Book participants commented that they were pleased to be assigned to the intervention group (even though they were not), which indicates that the control condition is sufficient for its intent—2-year longitudinal retention of the sample. Also, human contact is the same for both groups, and the time-on-task on the computer is unlikely to influence study knowledge and behavior endpoints.

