#### Data safety and monitoring

To ensure confidentiality, each participant is assigned a code number. All interviews and SCKnowIQ data are coded with the code number and linked to the participant’s name in order to display tailored intervention with the participant’s name. The participant’s name is removed from the database when statistical analyses are conducted. The demographic information and other self-report outcomes will be entered at a secure web site on a secure application server with data written to a secure database server that is maintained by the UF Health Sciences information technology (UF IT) group. No data remain, even temporarily, on the computer used by the participant. Access to the database server is restricted to the lead statistician and the principal investigator (as backup) and the programmer. The two servers (application and database) are backed-up nightly, and there is fire- and water-secure, offsite storage of backups. The UF IT systems are highly controlled to minimize privacy or data breaches. All applications undergo a stringent security and privacy evaluation before being deployed on the IT managed severs.

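### A single published block size of four in two strata makes up to a third of assignments predictable if registering staff learn the earlier ones; varied, undisclosed block sizes would remove nearly all of that at little cost

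*Protocol article*

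**What the plan says.** The Randomization section of the protocol article sets out the method. "Randomization to e-Book and CHOICES groups will be stratified by SCD and SCT", which gives two strata, and then: "Within each stratum, permuted block randomization with a block size of four will be performed to ensure group balance". No variation in block size is mentioned.

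The same section describes the safeguard. The statistician produces the allocation and the programmer implements it. For everyone else: "All other team members will be blind to the group assignment with no access to the electronic group assignment table within the software application".

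Screening and consent, together with Procedures, describe how a person enters. The research specialist speaks to each person by phone, receives the document confirming sickle cell status, approves the person and registers them. Only then does allocation happen: "The software application randomizes the participants based on registration information after verified by the RS".

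The Intervention section gives the length of each program in the preliminary work. For CHOICES: "Participants completed the intervention in 71.8 ± 28.7 minutes". For the control: "the e-Book was completed at an average of 8.6 ± 2.8 minutes at baseline". Only CHOICES has tailored boosters and nudges.

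**The concern.** A small fixed block can be worked out by anyone who knows its size and learns some of its assignments. In a block of four with two per arm, the fourth assignment is settled by the first three. The third is also settled whenever the first two match. The size is public, and there are only two sequences to follow.

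This matters when the person who controls entry might also learn earlier assignments. The research specialist's approval and registration come immediately before allocation, so the role can affect when a person enters and, to a limited degree, whether. The stated safeguard is denial of access to the table. That does not by itself prevent staff from learning an arm from what a participant says, or from how long a session took.

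If entry were timed to a predicted arm, the groups could differ in motivation from the start. Knowledge is measured at baseline, so an imbalance in it would be visible and could be adjusted for. Motivation is not measured, and the behavior outcome is self-reported.

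**Working it through.** **Plan's own figure.** The article gives no figure for predictability. The number randomized does reproduce: 430 / (1 − 0.15) = 505.9, so 506. The planned half-and-half split of SCD and SCT gives 506 / 2 = 253 per stratum.

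**Inputs.** Block size 4, 1:1, two strata (Randomization). 506 to be recruited (Setting and sample). The share q of earlier assignments that registering staff learn before the next registration in that stratum is not in the article. It is an assumption, taken over its whole range from 0 to 1.

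**Step 1: worst case, q = 1.** There are 6 equally likely orders of a 2:2 block.
- In 2 of them the first two assignments match, so the third and fourth are certain. In the other 4, only the fourth is certain.
- Expected certain assignments per block = (2×2 + 4×1)/6 = 1.333.
- Share = 1.333/4 = 33.3%, and 0.333 × 506 ≈ 169 people.
- Best-guess accuracy by position is 1/2, 2/3, 2/3 and 1, so 2.833/4 = 70.8%.

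**Step 2: partial knowledge.** Let each earlier assignment be learned independently with probability q.
- Third position certain: both earlier ones known and alike, q² × 1/3.
- Fourth position certain: all three known (q³), or exactly two known and alike (3q²(1 − q) × 1/3). The sum is q².
- Share certain = (q²/3 + q²)/4 = q²/3.

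| q | Certain in advance | Of 506 | Best-guess accuracy |
|---|---|---|---|
| 0 | 0% | 0 | 50.0% |
| 0.25 | 2.1% | 11 | 55.4% |
| 0.5 | 8.3% | 42 | 59.9% |
| 0.75 | 18.8% | 95 | 64.6% |
| 0.9 | 27.0% | 137 | 68.1% |
| 1 | 33.3% | 169 | 70.8% |

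**Step 3: alternatives, still at q = 1.** A larger fixed block helps only a little: 25% certain with size 6 and 20% with size 8. Randomly varied sizes were simulated with 253 per stratum and 400 replicates. The observer knew the possible sizes and every past assignment, but not the size of the current block.

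| Block sizes | Certain in advance | Best-guess accuracy |
|---|---|---|
| Fixed 4 | 33.3% | 70.8% |
| 4 or 6 | 5.4% | 69.2% |
| 4, 6 or 8 | 2.2% (about 11 of 506) | 68.0% |

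**Step 4: cost in balance.** If enrolment stops inside a block, the largest possible imbalance is half the block: 2 with blocks of four, 4 with blocks up to eight, in strata of about 253.

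**Step 5: how telling is program length, if seen?** Treat the published values as means and SDs of normal distributions and cut at 20 minutes. For CHOICES, (20 − 71.8)/28.7 = −1.80, so about 96% lie above. For the e-Book, (20 − 8.6)/2.8 = 4.07, so almost all lie below. About 98% would be classified correctly. This holds only for someone who can see program time.

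**The case against.** The strongest reply is that the article describes allocation by software, with the table withheld from all but the statistician and programmer. Data safety and monitoring adds: "Access to the database server is restricted to the lead statistician and the principal investigator (as backup) and the programmer". The research specialist is not on that list. If this works as described, q is 0 and nothing is predictable.

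A reader might infer that a specialist sees arm-revealing cues. The article does not say so:
- No section gives this role session times, delivery logs or payment triggers by arm, and the title denotes a role, not necessarily one person.
- The phone call comes before randomization and cannot reveal that person's arm.
- Payment amounts do not differ by arm, and the article states that staff contact is equal across arms.
- Boosters at 6 and 12 months and most monthly nudges would usually come after a block of four had closed.
- The 71.8 and 8.6 minutes are program times, not whole sessions. Adding about 25 minutes of measures at baseline and again at posttest gives roughly 122 versus 59 minutes, completed remotely.
- Many e-Book participants in the preliminary study believed that they were in the intervention group, so their remarks are an unreliable guide.

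Online screening and the required healthcare record also limit discretion over approval.

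All of this stands. It lowers the likely size of the problem but does not make the fixed size a good choice. Withholding the table closes one route to an assignment. A participant's mention of videos, or of how long the program took, is another, and the article does not address it.

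**Conclusion.** The point holds as an avoidable weakness in the stated method, not as a demonstrated failure of concealment. A single disclosed block of four is used where the arms are easy to tell apart and the registering role acts just before allocation.

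The size depends on q, which the article does not give. The figure of one third, about 169 of 506, is an upper bound that requires every earlier assignment in the stratum to be learned in time. It should not be read as the share that will be known. At q = 0.5 the figure is 8.3%, about 42 people, and at q = 0 it is nil. The q²/3 formula assumes that assignments are learned independently of one another and that the observer knows where each block starts.

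A reader might also infer that any resulting bias is beyond repair in the analysis. That is too strong: baseline knowledge is collected and can be adjusted for. What would remain is selection on motivation or similar traits that are not measured. The power figures do not bear on this point.

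**What to change.** In the Randomization section, replace the single block size with permuted blocks of randomly varying size, for example 4, 6 and 8, within the SCD and SCT strata. The statistician generates the list as now. The sizes should not be disclosed to registering staff or published while enrolment is open. If enrolment has begun, apply the change to the remaining list in each stratum.

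Add a sentence stating that staff who register participants cannot view session timing or intervention delivery logs while enrolment is open. This is at least as important as the block sizes. Varied sizes remove nearly all certain assignments but barely reduce how often a guess is right, whereas keeping cues away from staff lowers q itself.

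The cost is a few lines in the existing randomization code, a restriction on what those staff can see, and two protocol sentences. The slightly larger possible imbalance at the end is negligible in strata of about 253.
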